### Statistical Analysis

Descriptive statistics will be used to present baseline characteristics and results of outcome measurements. The main analysis will be an analysis of covariance (ANCOVA) with between-group factor Intervention (2 levels) and within group factor Time (3 levels). Baseline scores will be used as covariates. Two-sided 95% confidence intervals (CI) will also be calculated, as well as effect size (Cohen's d). *Post-hoc* Tukey test will be used to test for pairwise comparisons. The Benjamini–Hochberg procedure will be applied to control the false discovery rate (27). According to the Intention to treat (ITT) principle every randomized PwMS, including the drop-outs, will be included for final evaluation. Multiple imputation methods will be used to handle missing data, caused by random drop outs. For all analyses the level of significance will be set at *p* < 0.05. Statistical analyses will be performed using PASW for Windows (version 23.0; SPSS, Inc. Chicago, IL).

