## Methods and Design

### Trial Design

An observer-blinded RCT will be performed with random allocation of intervention, with pre- (baseline) and post-intervention measurements, at 4 weeks immediately after intervention and a follow-up 12 weeks later, after finishing the training. The study flow chart is shown in see Figure 1. Ethical approval has been given by the Ethics committee of the State of Luzern (EKNZ/2017-00768), Switzerland. Trial registration is Clinicaltrials.gov NCT03369470 and SNCTP clinical trials registry SNCTP000002451. The study will be performed according to the CONSORT (Consolidated Standards of Reporting Trials) statement, http://www.consort-statement.org/.

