### Sample Size Calculation

The significance level alpha is defined two-tailed at *p*-value of 0.05 for detecting 20% difference between groups on the Arm Function in Multiple Sclerosis Questionnaire (AMSQ) in favor of the App-based dexterity group. Based on mean expected baseline values of 50.2 ±14.0 (pooled mean and standard deviations values) of the whole group, a 20% difference would reflect a 10-point improvement. Following Cohen's guidelines (21), the probability to prevent type II error is set at 0.20 assuming a 1-beta value of 0.80. The power analysis (clinical superiority trial), with the above-mentioned parameters, resulted in a total sample size of 62 persons, i.e., 31 people per group. Considering a maximal drop-out rate of 10% we aim to recruit 70 patients in total.

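### The main ANCOVA uses baseline both as a Time level and as the covariate: a time-averaged treatment effect and its interval are scaled by 2/3 (p-value unchanged), and pooled-error comparisons get wrong standard errors

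*Protocol article*

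**What the plan says.** The Statistical Analysis section of the protocol article defines the main analysis as an ANCOVA with "between-group factor Intervention (2 levels) and within group factor Time (3 levels). Baseline scores will be used as covariates". It adds two-sided 95% confidence intervals, Cohen's d and Tukey post-hoc pairwise comparisons. It does not say which term carries the treatment comparison (Intervention main effect, Intervention by Time, or a visit contrast), nor which error term the Tukey comparisons use.

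The Trial Design section describes a trial "with pre- (baseline) and post-intervention measurements, at 4 weeks immediately after intervention and a follow-up 12 weeks later". The Abstract and the Randomization and Blinding section list the same three occasions. No fourth assessment appears anywhere.

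The Sample Size Calculation section sets the target: "a 20% difference would reflect a 10-point improvement", based on "mean expected baseline values of 50.2 ±14.0 (pooled mean and standard deviations values) of the whole group". It "resulted in a total sample size of 62 persons, i.e., 31 people per group".

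**The concern.** With three assessments in all, a Time factor of three levels has to count baseline as one of the repeated responses. The same section also puts the baseline score on the right-hand side of the model. Either choice alone is a standard analysis. Together they make one of the three responses perfectly predicted by the covariate.

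Two things are at stake. The first is the size of the reported treatment effect: a difference averaged over all three levels includes one that is zero by algebra, so readers would compare a diluted figure with the 10-point design target. The second is the precision of post-hoc comparisons: a pooled error term would include a level with no residual variance.

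**Working it through.** **Inputs.** From Sample Size Calculation: SD 14.0, difference 10 points (20% of 50.2 is 10.04), two-sided alpha 0.05, power 0.80, 31 per arm. From Trial Design and Statistical Analysis: three assessments, three Time levels, baseline as covariate. Assumed, because the article does not give them: correlations between visits (range below) and equal SD at every visit.

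**1. The plan's own figure.** n per arm = 2 × (1.960 + 0.842)² × 14² / 10² = 30.8, so 31 per arm and 62 in total. With 10% drop-out, 62 / 0.90 = 68.9, so 69, or 70 for equal arms. The stated numbers are reproduced. This calculation uses neither Time nor the covariate, so the point below does not change it.

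**2. The baseline level.** Regress Y0 (baseline) on group and Y0. The coefficient of Y0 is 1, the coefficient of group is 0 and every residual is 0. The adjusted group difference at this level is therefore exactly zero, with no residual variance.

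**3. The averaged effect.** Let d1 and d2 be the adjusted differences at 4 weeks and follow-up.
- Three levels: (0 + d1 + d2) / 3. Two post-baseline levels: (d1 + d2) / 2. The ratio is 2/3, whatever the correlations.
- d1 = d2 = 10: 20/3 = 6.7 against 10. With d1 = 10 and d2 = 5: 15/3 = 5.0 against 7.5.

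**4. Its test.** The standard error is scaled by the same 2/3, because the zero level adds no variance. In simulation (31 per arm, correlation 0.7, 4,000 trials) the mean benefit was 6.69 with SE 1.43 on three levels, and 10.04 with SE 2.14 on two. The mean absolute t was 4.73 for both, and within each trial the two t values agreed to rounding error. Null rejection was 0.047 to 0.057 over all scenarios.

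**5. Its interval.** With a true 10 points at both visits, the three-level 95% interval contained 10 in 50% of simulated trials at correlation 0.5 and in 37% at 0.7 (8,000 trials each). This is the 2/3 scaling again, not a second problem.

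**6. Single-visit group contrast.** The residual variance given baseline is V = 14² × (1 − r²), with r the baseline-to-visit correlation. Pooled over three levels it is (0 + V + V)/3 = 2V/3, so the SE is multiplied by √(2/3) = 0.816, about 18% too small.
- r = 0.5: V = 196 × 0.75 = 147. Correct SE √(2 × 147/31) = 3.08; pooled √(2 × 98/31) = 2.51. Simulation: 3.09 and 2.53.
- r = 0.7: simulation 2.55 and 2.09.
- Type I error: 2 × (1 − Φ(1.96 × 0.816)) = 0.11. Simulation over all scenarios: 0.10 to 0.12.
- With each visit's own residual variance the SE is right: 2.55 against an empirical SD of 2.59 at r = 0.7.

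**7. Other contrasts, with pooled within-subject error.** Let s be the visit-to-visit correlation and ρ = (s − r²)/(1 − r²) the residual correlation. Change from baseline has residual variance V at either visit; follow-up minus 4 weeks has W = 2V(1 − ρ). Pooling replaces each by P = (V + V + W)/3. SE ratios (pooled over correct) are √(P/V) and √(P/W); type I errors are simulated.

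| r / s | V | W | P | SE ratio, change from baseline | Type I | SE ratio, follow-up minus 4 weeks | Type I |
|---|---|---|---|---|---|---|---|
| 0.5 / 0.5 | 147.0 | 196.0 | 163.3 | 1.05 | 0.035 | 0.91 | 0.065 |
| 0.7 / 0.7 | 100.0 | 117.6 | 105.8 | 1.03 | 0.041 | 0.95 | 0.060 |
| 0.8 / 0.8 | 70.6 | 78.4 | 73.2 | 1.02 | 0.049 | 0.97 | 0.056 |
| 0.7 / 0.85 | 100.0 | 58.8 | 86.2 | 0.93 | 0.074 | 1.21 | 0.017 |

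The direction of the error depends on the contrast and on the correlations.

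**The case against.** The strongest reply is that the double use of baseline may do no harm in practice. The article does not say that the treatment effect will be read from the time-averaged main effect. Its aim speaks of short-term and long-term benefit, which points to visit-specific effects, and those are not shrunk: at a true 10 points, both the 4-week difference and the baseline-to-4-week Intervention by Time contrast come out at 10.0. Even for the main effect the significance test is unaffected. The standard-error problem needs a pooled error term, which a classical Tukey test would normally use but which the article does not state. All of this stands, and it limits the point.

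Four stronger readings are tempting and are not supported:
- That the main analysis loses power or has a wrong type I error. The main-effect t and p are identical with two or three levels.
- That every reported effect, including Cohen's d, is a third too small. This holds only for quantities built from the three-level average.
- That sphericity fails by construction. Unequal residual variances do follow by construction, but sphericity concerns variances of differences. It holds when the two post-baseline residuals have equal variance and correlation 0.5, for example r = 0.7 and s = 0.745: (0.745 − 0.49)/0.51 = 0.5.
- That all pooled-error comparisons are anti-conservative. The table shows both directions; the 11% applies to the single-visit group contrast only.

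The objection does not remove the inconsistency. The article itself fixes the number of Time levels and the covariate, and nothing else in it resolves the clash. This is not a detail left for an analysis plan to fill in.

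**Conclusion.** The model is wrong as written and should be corrected before analysis. The double use of baseline follows from the article's own text and needs no assumption.

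Its effect on the results is conditional. If the Intervention main effect over three levels is reported, the estimate and interval are exactly 2/3 of the post-baseline average (6.7 instead of 10 points under the design effect at both visits), with the p-value unchanged. If error is pooled over the three levels, a single-visit group contrast has its SE about 18% too small and a type I error of about 0.11, assuming equal variances at the two post-baseline visits. Other pooled contrasts had type I errors between 0.017 and 0.074 over the correlations tried, which are assumptions. Visit-specific estimates with their own residual variance are correct.

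**What to change.** Replace the description of the model with one of these, not both:
- Time with two levels (4 weeks, follow-up) and the baseline score of the same outcome as covariate. Report the baseline-adjusted group difference at each visit, using visit-specific or unstructured residual variance.
- Time with three levels, no baseline covariate, and the arms constrained to a common baseline mean.

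The same sentence should say which contrast carries the treatment comparison.

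The cost is one sentence in the Statistical Analysis section. It needs no new data, patients or procedures, and the sample size of 62, with 70 recruited, stays as it is.

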The aim of the present study will therefore be to investigate the effectiveness of a tablet app-based dexterity home-based intervention in MS (TAD-MS). The short and long-term benefits of this training program will be compared with a Thera-band® training program. For these purposes, an observer-blinded proof-of-concept RCT will be performed. We hypothesize that TAD-MS will improve dexterity, leading to improved ADL, and HrQoL in PwMS.

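### A Tukey test is named for pairwise comparisons although the only factor with more than two levels is within-patient; between-arm contrasts at 4 weeks and follow-up should be pre-specified instead

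*Protocol article*

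**What the plan says.** In the protocol article, Statistical Analysis makes the main analysis an ANCOVA with "between-group factor Intervention (2 levels) and within group factor Time (3 levels". Baseline scores are covariates. The section then adds: "Post-hoc* Tukey test will be used to test for pairwise comparisons". It also plans 95% confidence intervals, Cohen's d and the Benjamini-Hochberg procedure. It does not say which pairs the Tukey test covers or which error term it uses.

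The aim, at the end of Background, is between arms: "The short and long-term benefits of this training program will be compared with a Thera-band® training program". The Sample Size Calculation is also for one between-arm difference: "The significance level alpha is defined two-tailed at *p*-value of 0.05 for detecting 20% difference between groups" on the AMSQ, which "resulted in a total sample size of 62 persons, i.e., 31 people per group".

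**The concern.** Classical Tukey compares all pairs among several independent means with one common error variance. Three uses are possible here, and none fits well:

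- **Two arms.** There is one pair, so Tukey is the t-test and the sentence has no effect.
- **Three visits.** The means come from the same patients and are correlated, so the independence assumption fails.
- **Intervention-by-Time cells.** The same correlation is present. The critical value also pays for pairs that nobody needs, such as one arm at week 4 against the other arm at baseline.

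The omnibus model does not itself give the arm difference at 4 weeks and at follow-up, and Tukey is the only follow-up test named. Durability also matters to this trial: Background says that the earlier home programme lacked long-term efficacy. If a test of change between week 4 and follow-up is too conservative, failure to detect fading could be taken for lasting benefit.

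**Working it through.** **Inputs from the Sample Size Calculation.** Two-sided alpha 0.05, power 0.80, SD 14.0, difference 10 points (20% of 50.2 = 10.04), 31 per arm. The correlation between AMSQ visits, rho, is not given. I assume 0.3 to 0.8, equal between all pairs of visits, with a constant SD.

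**1. The plan's own figure.** n per arm = 2 × (1.960 + 0.842)² × 14² / 10² = 30.8, so 31 per arm and 62 in total, as stated. Power at 31 per arm is 80.3% (normal) or 79.0% (noncentral t).

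**2. Tukey on two arms.** The critical value is the studentized-range quantile divided by √2. For two means and 60 df it is 2.000, the same as the t-test. Power stays at 79.0%.

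**3. Between-arm standard error at one visit.** SE = 14 × √(2/31) = 3.56. The two arms contain different patients, so rho does not enter. In simulation with a cell-pooled error, the empirical SD of the difference was 3.54 to 3.55 against an estimated SE of 3.55 at rho 0, 0.5 and 0.8. Unadjusted type I error was 4.8% to 5.0%.

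**4. Visit-to-visit standard error within one arm, raw scores.** An independent-groups error gives 3.56. The correct value is 14 × √(2(1 − rho)/31), so the ratio is 1/√(1 − rho).

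| rho | Correct SE | Independent-groups SE / correct SE |
|---|---|---|
| 0.3 | 2.98 | 1.20 |
| 0.5 | 2.51 | 1.41 |
| 0.7 | 1.95 | 1.83 |
| 0.8 | 1.59 | 2.24 |

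With a three-level Tukey test on this error, the simulated family-wise null rejection rate is below 2% at rho 0.3 and below 0.5% from rho 0.5 upward, instead of 5%. Power for a 10-point within-arm change is 70% to 83% over this range, against 92% to about 100% for a paired test.

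If the error were instead the residual variance after baseline adjustment, 14² × (1 − rho²), the ratio for week 4 against follow-up would be √((1 − rho²)/(1 − rho)) = √(1 + rho), or 1.14 to 1.34. The direction is the same and the size smaller.

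**5. Between-arm power at one visit, baseline covariate throughout.** Residual SD = 14 × √(1 − rho²), that is 12.1 at rho 0.5 and 10.0 at 0.7. Noncentrality = 10 / (residual SD × √(2/31)), that is 3.25 and 3.94.

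| Family | Critical value | rho 0.5 | rho 0.7 | rho 0.8 |
|---|---|---|---|---|
| Single contrast | 2.000 | 89% | 97% | 99.6% |
| Tukey, 4 post-baseline cells | 2.605 | 74% | 91% | 98% |
| Tukey, 6 cells | 2.881 | 64% | 85% | 96% |

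Without the covariate the three rows would be 79%, 58% and 47.5%, but the plan does adjust for baseline.

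**The case against.** The strongest reply is that the article makes Time a within factor and never says that visits are treated as independent. A studentized-range adjustment can be applied to contrasts from a fitted repeated-measures model, and an article may leave the error term and the family to the analysis plan. This stands as a limit: steps 4 and 5 are conditional. It does not rescue the sentence, because the choice of Tukey is stated and has no use in this design in which it is both needed and valid in its classical form.

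A reader might infer that the short- and long-term comparisons get wrong standard errors and therefore lose most of the stated 80% power. The documents do not support that. Those comparisons are between arms, and step 3 shows their standard errors are sound. The 80% belongs to a single between-arm difference and reproduces. Any loss arises from the critical value of a four- or six-cell family that the article does not state. Setting 47% against 89% would also mislead, since it drops the planned covariate from one side only.

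It is also true that Tukey is labelled post-hoc, that confidence intervals and effect sizes are planned as well, and that an over-conservative test adds no false positives.

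**Conclusion.** The point holds as a poorly chosen, under-specified method. Tukey is redundant for the two arms and unsuited to the within-patient factor.

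- With an independent-groups error, tests of change over time are too conservative: standard errors are 1.2 to 2.2 times too large on raw scores, or 1.14 to 1.34 times on baseline-adjusted residuals, for assumed correlations of 0.3 to 0.8.
- With a four- or six-cell family, between-arm power falls from 89% to 74% or 64% at an assumed correlation of 0.5, and from 97% to 91% or 85% at 0.7. At 0.8 the loss is small.

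The article does not support a claim that the sample size is wrong or that the between-arm tests are invalid. All correlations are assumptions, as is the equal-correlation structure.

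**What to change.** Delete the Tukey sentence in Statistical Analysis. In its place:

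1. Pre-specify two baseline-adjusted between-arm contrasts, at 4 weeks and at follow-up, each with a 95% CI. Estimate them from the repeated-measures model using the within-patient covariance.
2. Test any change from week 4 to follow-up as a contrast from the same model, preferably as a between-arm difference in change.
3. Apply the already planned Benjamini-Hochberg procedure to this stated set.

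The cost is a small change of wording and a model call, with no new patients or data. Other cell-by-cell comparisons are no longer tested, but they do not serve the aim.

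The 89% in the working is for one unadjusted contrast. Under Benjamini-Hochberg on three contrasts, the threshold for any one lies between 0.05/3 = 0.0167 and 0.05. At 0.0167 the critical value is 2.463 (60 df), and power is 78% at an assumed correlation of 0.5 and 93% at 0.7. Even this least favourable case stays above the four- and six-cell Tukey figures.

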### Availability of Data and Materials

In accordance with Good Clinical Practice Guidelines members of the ethics committees will be granted access to the original clinical data (coded) for audits or inspections, via the principal investigator. Throughout the entire study, strict confidentiality is ensured. All data will be coded and archived at the Luzerner Kantonsspital throughout the whole study period and archived for 15 years. All measurements (AMSQ, 9HPT, CRT, Jamar, MSIS-29), which are specifically related to the study design, will be entered directly into electronic Case Report Forms (eCRF).

## Discussion

Impaired dexterity is a frequently reported problem in MS, leading to reduced HrQoL (2, 4, 7). However, evidence-based upper limb therapies are still scarce mainly due to lack of methodologically well-conducted trials in this neglected field (4). New technology such as tablet app-based training, has been shown to improve working memory in MS (18).

The aim of the present proof-of-concept RCT is to investigate the effectiveness of a tablet app-based dexterity training at home, compared with a non-dexterity focused Thera-band® program. The exercises within the TAD-MS intervention focus on different components of dexterity such as pinch grip, coordinated finger movements, consequently being highly specific to improve dexterity. In addition, all exercises are game-based and designed to be challenging and to trigger motivation. During the performance of the dexterity exercises the app provides direct feedback of performance which can lead to immediate perception of error and correction of movement, increasing the effectiveness of progressive motor learning training (28, 29). Instead, the Thera-band® program includes non-specific upper limb and hand strength exercises.

The total dosage of the TAD-MS intervention is 600 min of dexterity training (30 min five times a week, 4 weeks), representing a trade-off between feasibility and adequate dosage. Although no studies have investigated tablet-app based dexterity training in MS, a previous home-based sensory re-education training (3 weeks, five times a week 15 min, 300 min total training) induced significant in manual dexterity (30), with stronger effect size when compared with another dexterity interventions (4) Additionally, another home-based dexterity program achieved adequate effect sizes with a 4-week program and 600 min of dexterity training (14). Therefore, the choice of the dosage of our TAD-MS seems appropriate to significantly improve dexterity. The TAD-MS has the potential to be easily implemented in the daily routine of PwMS, since no extensive instruction is needed and the program is not time consuming. Furthermore, TAD-MS is efficient in terms of staff resources as patients can train independently at home without continuous guidance from a therapist. Such cost-effectiveness should be investigated in future studies.

In sum, we expect that the presented tablet app-based program, TAD-MS, through provision of challenging, stimulating dexterity training in the patients' home-environment will be effective in PwMS.

## Dissemination

When protocol amendments are needed (e.g., to include another participating center), ethical approval will be obtained first. After having obtained this approval, relevant adaptations will be made in the relevant clinical trial registry databases.

After completing recruitment, according to the inclusion and exclusion criteria, statistical analyses are planned. When completed, submission to a peer-reviewed journal is planned. In addition, results will be published in patient and healthcare professional magazines and will be presented at national and international congresses.

## Abbreviations

Abbreviations: MS: Multiple Sclerosis
ADL: Activities of daily living
RCT: Randomized controlled trial
AMSQ: Arm Function in Multiple Sclerosis Questionnaire
MSIS-29: Multiple Sclerosis Impact Scale 29
9-HPT: Nine-hole peg test
CR: Coin rotation
PT: Physical therapy
HrQoL: Health related Quality of life
CI: confidence interval
ITT, Intention to treat CRF: Case Report Form
PwMS: Patients with Multiple Sclerosis.
